### Health economic evaluation

The objective of the economic evaluation is to estimate the cost-effectiveness of the intervention in terms of additional costs per additional resident not receiving an antipsychotic prescription. The economic evaluation will be performed from the perspective of the German social insurance (statutory health insurance and long-term care insurance). To this end, an incremental cost-effectiveness ratio (ICER) will be calculated, i.e. the ratio of the difference in costs between intervention and control group divided by the difference in the proportion of residents without a psychotropic medication gained in each group.

A detailed description of the health economic evaluation can be found in Additional file 1.

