## Trial objective

The aim of our study is to investigate whether a PCC approach, successfully evaluated in nursing homes in the United Kingdom [35], can be implemented in German nursing homes and, in comparison with a control group, can result in a clinically relevant reduction of the proportion of residents with antipsychotic prescriptions. Our *primary outcome* is the proportion of residents with at least one antipsychotic prescription (long-term medication) after 12 months of follow-up.

A further aim is to investigate whether QoL will improve or at least be unchanged as shown by Fossey et al. [35]. In accordance with the results of the primary efficacy study and a Cochrane review [33], we assume that the intervention is not only effective but also does not harm the residents, i.e. dementia-related BPSD will not worsen in the intervention group, and prescription rates of other psychotropic medication as well as the application of physical restraints will not increase. Therefore, the following *secondary outcomes* will be evaluated (at 12 months):Presence of agitated behaviour,Residents’ QoL,Median daily dose of antipsychotics in chlorpromazine equivalents,Proportion of residents with dementia with antipsychotic prescription,Proportion of residents without dementia with antipsychotic prescription,Prescription prevalence of other psychotropic drugs (antidepressants, anxiolytic and hypnotic drugs, acetyl-cholinesterase inhibitors),Safety parameters are number of falls, fall-related fractures and sutures, fall-related medical attention as well as the proportion of residents with at least one physical restraint (bilateral bedrails, belts, fixed tables, and other measures limiting free body movement), and the number and types of physical restraints.

Additionally, a health economic evaluation will be conducted alongside the study. A process evaluation will also be performed, aiming to comprehensively analyse the underlying processes as well as the barriers and facilitators of the implementation of this multicomponent intervention, giving special focus to regional differences. The programme will be implemented in nursing homes in East, North, and West Germany in order to evaluate its supra-regional generalisability.

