### Sample size calculation

The primary endpoint of the study is the proportion of residents with at least one antipsychotic prescription after 12 months (t_4_). The following sample size estimation was performed as described in Donner & Klar [57] for the cluster-adjusted *χ*^2^-test. Based on recent prevalence data, we expect a baseline prevalence of antipsychotic prescription of 30 % [2]. Due to the measures of optimised usual care in the control group and based on the study by Fossey et al. [35], we expect the prevalence in the control group to decline slightly to 26 % after 12 months. We expect a relative risk reduction of approximately 50 % regarding antipsychotic prescription in the intervention group.

Assuming a significance level of 5 % (α = 0.05), a two-sided test for proportions, and an intra-class correlation coefficient (ICCC) of 0.05, an average cluster size of 65 nursing home residents, 15 clusters are required per group to detect a 12 % difference in proportions from 26 % of the control group at 12 months with 90 % power (β = 0.10). Presuming that six nursing homes might drop out, 36 clusters with a total of 2340 residents will be needed.

We expect 25 % of residents with early study termination due to death or moving; the other 75 % of residents of the baseline population we expect to be still living in the nursing home and to be available for the 12-month follow-up assessment. As the outcome, the analyses will focus on the group of residents living in the nursing homes after 12 months. Assuming that new residents will all be willing to participate in the study, this will not affect the sample size.

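### The ICER formula counts residents free of any psychotropic, while the stated economic objective counts residents free of antipsychotics

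*Protocol article*

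**What the plan says.** The Health economic evaluation section of the protocol article gives the aim as estimating "additional costs per additional resident not receiving an antipsychotic prescription". After a sentence on the payer perspective, it introduces the ICER as the means to that aim and defines it as the between-group difference in costs "divided by the difference in the proportion of residents without a psychotropic medication gained in each group". For details it refers to Additional file 1.

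The Trial objective section shows that the two drug terms are not interchangeable. It lists as a separate secondary outcome "Prescription prevalence of other psychotropic drugs (antidepressants, anxiolytic and hypnotic drugs, acetyl-cholinesterase inhibitors"; the word *other* makes antipsychotics one member of a larger class. The same section assumes that "prescription rates of other psychotropic medication as well as the application of physical restraints will not increase". The Measures section also keeps the two apart: antipsychotic prescriptions are collected retrospectively over three months, other psychotropics as current prescriptions at each measurement point.

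The Sample size calculation section states: "The primary endpoint of the study is the proportion of residents with at least one antipsychotic prescription after 12 months". No section defines an outcome of being free of all psychotropics.

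**The concern.** An ICER is only as meaningful as the effect unit in its denominator. Here the objective and the formula name different units. The objective's unit matches the primary outcome and the drug class that the intervention targets; the medication review, for instance, is given only to residents with an ongoing antipsychotic prescription. The formula's unit is freedom from a broader set of drugs, for most of which the protocol assumes only that use will not rise.

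An analyst who followed the formula literally would report a ratio that does not answer the stated question and does not use the trial's primary effect. If the wording stays as it is, either version could also be defended after the results are known, and the two could give quite different figures.

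**Working it through.** **Inputs from the protocol article.** Sample size calculation: control proportion 26 % at 12 months, planned difference 12 points (hence 14 % under intervention), two-sided α = 0.05, power 90 %, intra-class correlation 0.05, average cluster size 65, 15 clusters per group. No cost figure and no prevalence of co-prescription is given.

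**Step 1: the plan's own figure.** This only confirms that 12 points is the planning value for an antipsychotic-based denominator.

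- Per arm, ignoring clustering: n = [1.96 × √(2 × 0.20 × 0.80) + 1.28 × √(0.26 × 0.74 + 0.14 × 0.86)]² / 0.12², which rounds up to 232.
- Design effect: 1 + (65 − 1) × 0.05 = 4.2.
- Clusters per group: 232 × 4.2 / 65 = 14.99, so 15. The stated figure reproduces: "15 clusters are required per group to detect a 12 % difference in proportions from 26 % of the control group at 12 months".

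**Step 2: how the two denominators relate.** Let A be use of an antipsychotic and O use of another psychotropic. A resident is on some psychotropic if on A, or on O without A:

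P(A or O) = P(A) + P(O without A).

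Writing I for intervention and C for control:

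gain in psychotropic-free residents = gain in antipsychotic-free residents − [P_I(O without A) − P_C(O without A)].

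The bracket is where the definitions part. It grows whenever a resident leaves antipsychotics and is still taking, or is newly given, another psychotropic.

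**Step 3: illustration.** Assume that a share s of the residents who come off antipsychotics keep or start another psychotropic, and that nothing else changes. The bracket is then 0.12 × s, so the formula's denominator is 0.12 × (1 − s). For the same cost difference, the ICER is larger by 0.12 / [0.12 × (1 − s)] = 1/(1 − s). The last column uses an arbitrary cost difference of 100 per resident.

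| s (assumed) | Denominator in the formula | ICER factor | ICER at cost difference 100 |
|---|---|---|---|
| 0 | 0.12 | 1.00 | 833 |
| 0.25 | 0.09 | 1.33 | 1,111 |
| 0.50 | 0.06 | 2.00 | 1,667 |
| 0.75 | 0.03 | 4.00 | 3,333 |

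Under this model the definitions agree only at s = 0, that is, if nobody who comes off antipsychotics keeps or starts another psychotropic. As s nears 1 the denominator nears zero and the ratio becomes unstable.

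**Step 4: does the assumption about other psychotropics remove the conflict?** No. Total use of O can stay flat while residents move from taking both A and O to taking O alone. Each such resident adds to the gain in antipsychotic-free residents and nothing to the gain in psychotropic-free residents.

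**The case against.** The strongest reply is that the intended reading is clear. The formula is presented as serving the objective stated just before it, antipsychotic prescription is the primary outcome throughout, and no psychotropic-free outcome is defined anywhere. This looks like a wording slip in a short summary, and the working description is in Additional file 1. Most of that stands, and it lowers the chance that an analysis would go wrong. It does not remove the contradiction, because the slip is in the sentence that defines the ratio and nothing shown reconciles it with the objective.

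A second reply is that nothing else in the trial is touched. That also stands. The primary test and sample size do not depend on this sentence, and prescriptions of both kinds are collected at 12 months, so either denominator can be computed.

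Three stronger readings are tempting but not supported:

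- A reader might infer that the detailed economic plan contains the same error. That file is not shown, so one can only ask for it to be checked.
- A reader might infer that a successful intervention would appear to have no effect. The Statistical analysis section has the antipsychotic difference tested and reported with its own cluster-adjusted confidence interval, so the ratio could mislead but could not hide that result.
- A reader might infer that the ICER would double. That factor belongs to an assumed s of 0.50; the documents support no particular value.

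**Conclusion.** The point holds as an internal contradiction in the Health economic evaluation section. As written, the formula does not deliver the stated objective and does not use the primary-outcome difference. On the planned 12-point effect, the ICER would be overstated relative to the objective's definition by 1/(1 − s): from no change at s = 0 to fourfold at s = 0.75. These factors rest on the assumed share s and on nothing else changing between groups; the protocol article gives no figure that would narrow the range. The correction is of moderate weight and concerns the economic evaluation only.

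**What to change.** In the ICER sentence, replace *without a psychotropic medication* with *without an antipsychotic prescription*, so that the denominator matches both the stated economic objective and the primary outcome. Check that Additional file 1 uses the same definition, and align it if it does not. If a ratio based on freedom from all psychotropics is also wanted, name it as a separate analysis with its own label.

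The cost is a change of a few words and one cross-check, best made before the economic analysis begins. No additional data, recruitment or change to the primary analysis is needed.

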### Sample size calculation

The primary endpoint of the study is the proportion of residents with at least one antipsychotic prescription after 12 months (t_4_). The following sample size estimation was performed as described in Donner & Klar [57] for the cluster-adjusted *χ*^2^-test. Based on recent prevalence data, we expect a baseline prevalence of antipsychotic prescription of 30 % [2]. Due to the measures of optimised usual care in the control group and based on the study by Fossey et al. [35], we expect the prevalence in the control group to decline slightly to 26 % after 12 months. We expect a relative risk reduction of approximately 50 % regarding antipsychotic prescription in the intervention group.

Assuming a significance level of 5 % (α = 0.05), a two-sided test for proportions, and an intra-class correlation coefficient (ICCC) of 0.05, an average cluster size of 65 nursing home residents, 15 clusters are required per group to detect a 12 % difference in proportions from 26 % of the control group at 12 months with 90 % power (β = 0.10). Presuming that six nursing homes might drop out, 36 clusters with a total of 2340 residents will be needed.

We expect 25 % of residents with early study termination due to death or moving; the other 75 % of residents of the baseline population we expect to be still living in the nursing home and to be available for the 12-month follow-up assessment. As the outcome, the analyses will focus on the group of residents living in the nursing homes after 12 months. Assuming that new residents will all be willing to participate in the study, this will not affect the sample size.

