#### Recruitment of study centres and study participants

In each study region, nursing homes will be randomly selected from the respective nursing home register. These facilities will be invited to take part in the study either via postal mail or telephone. The study will be presented to the directors of the nursing homes, who will decide whether their home will participate. A resident representative or, if not available, a residents’ advocate will be involved in all activities and decisions.

All eligible residents or their proxies or legal guardians will receive oral and written information about the aims and purpose of the study as well as all the information required according to good clinical practice (GCP) rules to create informed consent. Questions and additional information about the study will be available from the project staff of the respective study centre, either in person or by phone. Consent may be withdrawn for any reason at any time and without notice, without incurring any disadvantages for the residents. All residents who move into the nursing home during the study period will be eligible to participate too and will be asked for consent.

A total of four nursing homes (two facilities each in the intervention group and in the control group) will take part in a controlled pilot study at the study centre in Halle (Saale). The study will be implemented respectively in recruiting phases of four nursing homes per study site with a time shift of 2 months. The data collection will end in the last quarter of 2016.

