### Cluster-randomisation

The randomisation will be carried out on a cluster level. The randomisation list will be computer-generated by an independent external biometrician, who will be blinded to the identity of the participating organisations and residents. Nursing homes will be allocated to the intervention or control group using a balanced block randomisation, stratified by the three regions Halle (Saale), Lübeck, and Witten as well as the time point of the recruiting phase. Because of the low number of homes per stratum (*n* = 4), no further blocks within the strata are planned. This randomisation list will contain pseudonymous identification numbers for nursing homes and allocation of group A or B.

Parallel to this, responsible coordinators of the three study centres will independently determine and document the allocation (intervention group or control group) for group A and group B at study begin, without informing the external biometrician.

After completion of the baseline measurement of the corresponding recruiting phase, an independent person from the study centre in Lübeck will electronically (password-protected, encoded https portal) assign the randomisation list and nursing home data for concealed allocation [44] and will inform the nursing homes in written form. After confirmation of group allocation by the nursing homes, the assigning person will inform the coordinator of the respective study centre about the allocation results.

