New participants during the study period will be assessed at the next measurement point after their nursing home admission: socio-demographic and clinical data, QoL and cognition (QoL-AD, DSS), and agitated behaviour (CMAI) at this point will be regarded as baseline data of the new participant. Medication data and safety parameters since nursing home admission will also be documented retrospectively.

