### Statistical analysis

No interim analysis will be performed. Analysis will be based on the intention-to-treat principle. The analysis will be done at the resident level.

For the primary outcome measure, i.e. the proportion of residents with at least one antipsychotic prescription after 12 months, proportions will be compared between the intervention group and control group, using a two-sided cluster-adjusted *χ*^2^-test at a level of significance of α = 0.05 [57]. Corresponding cluster-adjusted 95 % confidence intervals will be calculated. Furthermore, to investigate the time course of the intervention effect, including all the residents observed after 3, 6, 9, or 12 months, drug prescriptions of antipsychotics per resident after 3, 6, 9, and 12 months will be analysed as a dependent variable in a generalised linear mixed (logistic) model with the intervention as a fixed effect, clusters as a random effect, and using covariance patterns to adjust for repeated measurement. This will be done as a secondary analysis.

For the secondary outcome measures, linear mixed models or generalised linear mixed methods will be used, adjusting for clusters by random effects. Subgroup analyses using linear mixed models will be performed for gender and cognitive status. The analysis of all secondary outcomes is interpreted exploratively and not confirmatively.

A detailed description of the statistical analysis can be found in Additional file 2.

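### The primary analysis is called resident-level intention-to-treat, but its 12-month set is about one quarter newcomers recruited after homes know their arm, and no analysis of the pre-randomisation cohort is stated

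*Protocol article*

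**What the plan says.** Under Statistical analysis, the protocol article states "Analysis will be based on the intention-to-treat principle" and "The analysis will be done at the resident level". The primary test is a two-sided cluster-adjusted chi-square test on the proportion with at least one antipsychotic prescription at 12 months, with no covariates.

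The analysed population is given under Sample size calculation: "the analyses will focus on the group of residents living in the nursing homes after 12 months". The same paragraph expects 25 % to be "residents with early study termination due to death or moving", and continues: "Assuming that new residents will all be willing to participate in the study, this will not affect the sample size".

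The recruitment section opens the study to later arrivals: "All residents who move into the nursing home during the study period will be eligible to participate too and will be asked for consent". Under Cluster-randomisation, homes are told their arm in writing, and allocation follows baseline: "After completion of the baseline measurement of the corresponding recruiting phase". The Blinding section says that home staff and field researchers cannot be blinded. Medication reviewers and primary-endpoint assessors are blinded.

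The safety parameters under Trial objective are falls, fall-related injuries and medical attention, and restraints. Death is not listed, although the Background cites increased mortality among antipsychotic users.

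**The concern.** In a resident-level intention-to-treat comparison, randomisation protects the contrast because the people compared were identified before allocation. The article delays allocation until baseline is complete, which gives the t0 cohort that protection. The 12-month set departs from it in two ways.

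- **Joiners.** Newcomers enter by admission and individual consent when the home already knows its arm. If intervention homes attract, admit or enrol people with a different chance of being on antipsychotics, the 12-month proportions differ without any effect on prescribing. The primary test has no covariates that could absorb this.
- **Leavers.** Residents who die or move are outside the primary set. If leaving is related to antipsychotic use differently in the two arms, the proportions among those who stay also differ without any effect on prescribing.

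At stake is whether a confirmatory difference can be read as a change in prescribing rather than partly a change in who is counted.

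**Working it through.** **1. The plan's own figure.** Inputs from Sample size calculation: 26 % against 14 % (a 12-point difference), two-sided α = 0.05, power 90 %, intra-class correlation 0.05, 65 residents per home.

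- Unadjusted n per arm (pooled variance, no continuity correction): 232.
- Design effect: 1 + (65 − 1) × 0.05 = 4.2.
- Homes per arm: 232 × 4.2 / 65 = 14.99, so 15.
- Total: (15 + 15 + 6) × 65 = 2340.

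The stated size reproduces. Power at 15 homes of 65 is 90.1 %. The sample size is not at fault.

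**2. Composition of the 12-month set.** With 25 % leaving and full replacement, as the plan assumes:

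- 36 homes: 0.25 × 2340 = 585 leavers outside the set and about 585 newcomers inside it.
- 30 homes (after the allowed loss of six): 0.25 × 1950 = 487.5, about 488.

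**3. Recruitment bias (assumed inputs, no true effect).** Let 75 % of the set be stayers at 26 % in both arms, and let newcomers' prevalence be lower in the intervention arm by d. The spurious difference is 0.25 × d. The effective n per arm is 15 × 65 / 4.2 = 232, which gives a standard error of about 4.0 points.

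| d (points) | Spurious difference (points) | Two-sided rejection, nominal 5 % |
|---|---|---|
| 5 | 1.25 | about 6 % |
| 10 | 2.5 | about 10 % |
| 16 | 4.0 | about 17 % |

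The document gives no value for d.

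**4. Survivor bias (assumed inputs, no true effect).** Suppose everyone leaves at 25 %, except antipsychotic users in the intervention arm.

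- Users leave at 35 %: prevalence among stayers is 0.26 × 0.65 / (0.26 × 0.65 + 0.74 × 0.75) = 23.3 %, a spurious 2.7 points.
- Users leave at 40 %: 21.9 %, a spurious 4.1 points.
- Users leave at 20 %: 27.3 %, 1.3 points against the intervention.

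These are differences among stayers. With a quarter of the set being newcomers at 26 %, they shrink to about 0.75 × 2.7 = 2.0, 0.75 × 4.1 = 3.1 and 0.75 × 1.3 = 1.0 points.

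**5. Power in the pre-randomisation cohort.** Residents per home: 65 × 0.75 = 48.75. Design effect: 1 + 47.75 × 0.05 = 3.39.

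- 15 homes per arm: effective n = 15 × 48.75 / 3.3875 = 216, power 87.9 %.
- 18 homes per arm: effective n = 18 × 48.75 / 3.3875 = 259, power 92.9 %.
- Homes per arm for 90 %: 232 × 3.3875 / 48.75 = 16.1, so 17. As a primary analysis this would cut the spare homes from 6 to 36 − 34 = 2.

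**The case against.** The strongest reply is that homes are randomised, that the endpoint is prescription prevalence at 12 months, and that an open-cohort cross-section is a proper target for a home-level intervention. A resident who has died or moved has no 12-month prescription in that home. The population and its turnover are stated openly, and nothing suggests that homes are analysed outside their allocated arm. This stands. It is why the cross-section can remain primary, and why the fault lies in the label and in the missing check.

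Two further replies carry less weight. Blinded endpoint assessment limits ascertainment bias, but does not affect who is admitted, enrolled, moved or dies. The assumption that every newcomer joins would rule out selection by consent, but not by admission, and the plan cannot enforce it.

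Additional file 2, which holds the detailed statistical analysis, is not at hand and may already contain such analyses. The article, however, itself fixes the analysed set, the newcomer rule and the intention-to-treat label.

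A reader might infer more than the documents support:

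- **That survivor bias is demonstrated.** If users leave 1.3 to 1.6 times as often as non-users, with 25 % leaving overall, a true 26 % appears as 24.2 % to 22.7 % among stayers. If this holds in both arms, the difference between arms is still zero.
- **That newcomers' late baseline contaminates the analysis.** Their first assessment "at this point will be regarded as baseline data of the new participant", and for admissions after the 9-month point it coincides with the 12-month outcome. But the article states no adjustment for baseline values.
- **That falls of leavers are discarded.** Falls and fractures are collected every 3 months for the preceding 3 months, and nothing says that records of residents who later leave are dropped.
- **That a closed cohort should replace the primary analysis.** It still conditions on survival to 12 months, loses the dilution by newcomers, and costs power.

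**Conclusion.** The concern holds in a limited form: it should be fixed, but it does not invalidate the design. The set described is an open-cohort cross-section carrying a resident-level intention-to-treat label. On the plan's attrition and replacement assumptions, about a quarter of it is recruited after allocation is known.

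The direction and size of any recruitment bias cannot be derived from the document. The illustrative 1.3 to 2.5 points is small beside the 12-point target. It would matter more if the true effect were well below plan. Survivor bias in the contrast requires leaving by antipsychotic users to differ by arm, for which the document gives no evidence. Comparing deaths and moves by arm is worthwhile for that reason, and because mortality is named as a harm but not listed as an outcome.

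**What to change.** - **Describe the estimand.** Keep the 12-month cross-section as primary, and call it an open-cohort, home-level comparison with homes analysed as randomised.
- **Prespecify the key sensitivity analysis.** Run the same test in residents consented and assessed at t0, before randomisation, and present at t4. State that it removes recruitment bias but not survivor bias.
- **Use the home-level proportion as a further check.** The proportion among all eligible residents, already recorded at baseline and 12 months under Institutional level, addresses selection by consent. It does not address selection by admission.
- **Report flow by arm.** Compare deaths and moves in all t0 residents, and give newcomer numbers and consent rates.
- **State the safety set.** Analyse falls and fractures in all residents with time at risk, including those who later leave or die.

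If Additional file 2 already contains any of this, the article need only point to it and correct the label. The cost is a few extra analyses, nearly all of data already collected; newcomer consent rates also need a count of those approached. Power of the primary test is unchanged. The sensitivity analysis has about 49 residents per home and the power shown above. Only the pilot phase has started, so the change can still be made before outcome data exist.
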